### Economic evaluation

Incremental cost-effectiveness analysis is to be undertaken to determine whether the intervention represents “value for money” compared to the “usual care” control. The economic evaluation is conducted from a limited societal perspective, using detailed pathway analysis to specify all relevant intervention activities and costs. A detailed accounting of resource use required to deliver the two arms in the trial is undertaken to allow accurate costing of the interventions. The limited societal perspective incorporates cost impacts on government as the provider of healthcare services, healthcare costs to individuals and costs to workplace organisations. The intervention is costed assuming it is in ‘steady state’ (i.e. excluding research-related costs).

Additionally, a within-trial economic evaluation is to be undertaken as a cost-consequence analysis, comparing the costs of the intervention with the primary outcome measures (e.g. cost per change in HbA1c) at 6 months and 12 months timepoints. A modelled economic evaluation is to be undertaken, extrapolating intervention costs and effects and extending the target population, time horizon and decision context. The model will be extrapolated to lifetime to incorporate benefits accruing to both T2D and dementia prevention. As 5 years is insufficient to observe outcomes of dementia in a prevention study, the intermediate outcomes of the trial (cognitive function, neurotrophic factors and inflammatory markers) will be incorporated.

into final outcomes for economic evaluation, e.g., dementia diagnosis, time to dementia.

Incremental health benefits, reported as quality-adjusted life years (QALYs) saved, and incremental healthcare cost offsets attributable to T2D prevention and dementia are reported. The commonly accepted cost-effectiveness threshold of AUD$50,000 per QALY saved will be used to determine cost-effectiveness over the lifetime. Utility is calculated from the Assessment of Quality of Life AQOL-8D using the Australian algorithm [112] and multiplied using the area under the curve method by the time in the trial to derive the QALYs.

Finally, an incremental cost-effectiveness ratio will be determined by calculating the difference in cost between the intervention and usual care, divided by the difference in QALYs between intervention and usual care.

### Statistics

#### Sample size

With an estimated 20% attrition based on our previous intervention trials, 2-tailed significance of 2.5% (correcting for two primary outcomes for the original OPTIMISE protocol), 125 participants per group (250 total) are required for 80% power to detect minimum differences of interest in HbA1c and sitting of 0.5% and 0.5 h/16 h-day, assuming standard deviations (SD) of 1.6 and 1.3 and a pre-post correlation (r) of 0.7 and 0.6 respectively. A 0.5% HbA1c decrease is clinically meaningful corresponding to to an approximate 10% reduction in diabetes-related mortality [7]. Assumptions concerning attrition, SD and r for primary and most secondary outcomes were based on Living Well with Diabetes [77], AusDiab [66] and Stand Up Victoria [76] studies. Recruitment projections indicate that a sample of 250 participants is feasible within the allocated timeframe. Recruitment will stop when the trial reaches either the required sample size or the maximum number of participants who can be recruited in the trial’s allotted recruitment timeframe, while complying with the unforeseeable restrictions and conditions related to the COVID-19 pandemic.

The sample size for the cognitive function outcomes are dictated by the original sample size calculations described above. From a sample size of 250, we anticipate 160 participants (80 in each arm) will complete the 12-month assessment. This sample size of 80 per group provides > 80% power (5% 2-tailed significance) to detect our minimum difference of interest in the primary outcome of visual memory (PAL TEA) at 12 months (1/3 SD, d = 0.33) assuming r = 0.7, based on a previous trial [113]. Changes in cognitive function have been detected in a similar sample with 145 participants participating in a 24-week RCT assessing pharmacotherapy to improve metabolic control. Minimum detectable differences will be recalculated if the actual sample size is lower than projected due to the potential impact of the COVID-19 pandemic.

#### Statistical analyses

Outcomes are all continuous and expected to be either normal or log-normal, in which case log-transformation will be used. Analyses will be performed in STATA version 15 or higher. Significance is set at *p* < 0.05 two-tailed (except for *p* < 0.025 when testing co-primary outcomes based on α = 0.025). To test the differences between groups in primary and secondary outcomes during (3 months), end of the intervention (OPTIMISE; 6 months) and end of the extended maintenance phase (12 months – OPTIMISE-extended) mixed models statistical analysis will be employed, accounting for repeated measures, adjusting for baseline values, randomisation strata, and potential confounders. Within-group changes for intervention participants occurring during the no health coaching contact phase from 12 to 18 months will be tested and compared to intervention phases. Within-group changes will also be tested in the delayed intervention participants receiving the OPTIMISED intervention after 12 months, at the 18 month timepoint, using paired t-tests (or non-parametric paired tests). Possible confounders will be identified a priori from the literature and narrowed down to a number that can be modelled without overfitting, based on an objective criterion not open to manipulation (backwards elimination: retaining age, sex, and *p* < 0.2 association with the outcome). Analyses will follow intention-to-treat principles. Sensitivity to handling missing data will be evaluated by comparing results from the main analyses (evaluable case analysis for mixed models; complete-case analysis for t-tests) with alternative methods that are appropriate for different missing data scenarios (e.g., multiple imputation; selection-covariate adjustment). Descriptive statistics will be used to describe the implementation indicators of the different phases of the intervention.

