### Primary outcomes

The primary outcomes are overall daily sitting time, and glycosylated haemoglobin (HbA1c) at 6 months, which were originally chosen in order to evaluate the intensive phase of the intervention (OPTIMISE). With the addition of the expanded protocol, cognitive function measures: visual learning and new memory (Paired Associates Learning Total Errors [adjusted]) were added as a primary outcome at 12 months.

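### Testing 6-month HbA1c and sitting each at a fixed 0.025 is valid and gives the stated power, but a Holm step-down would give more power from the same participants under the same 5% bound

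*Protocol article*

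**What the plan says.** Under Primary outcomes, the protocol article names the pair concerned: "The primary outcomes are overall daily sitting time, and glycosylated haemoglobin (HbA1c) at 6 months". The Sample size section plans at "2-tailed significance of 2.5% (correcting for two primary outcomes for the original OPTIMISE protocol" and claims "80% power to detect minimum differences of interest in HbA1c and sitting of 0.5% and 0.5 h/16 h-day". The variability behind this claim is set by "assuming standard deviations (SD) of 1.6 and 1.3 and a pre-post correlation (r) of 0.7 and 0.6 respectively". The section concludes that "125 participants per group (250 total) are required".

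The Statistical analyses section carries the same threshold into the tests. General significance is p < 0.05 two-tailed, with p < 0.025 "when testing co-primary outcomes based on α = 0.025". No step-down rule or passing-on of alpha is attached to this. I read the 0.025 as belonging to the two 6-month outcomes, because the Sample size section ties the 2.5% to them and powers the third primary, PAL TEA at 12 months, at 5%.

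**The concern.** The protocol fixes a decision rule here; it does not leave a gap for an analysis plan to fill. Under that rule each outcome faces 0.025 regardless of the other's result. Suppose sitting gives p = 0.001 and HbA1c p = 0.03. HbA1c is then declared not significant, although a procedure with the same 5% familywise bound would allow the claim.

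Holm rejects whenever Bonferroni rejects and sometimes when it does not. It needs no assumption about the correlation between the outcomes. What is at stake is power on two primary outcomes, above all HbA1c, which has the lower planned power and determines the sample size.

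**Working it through.** **Inputs, all from the Sample size section.** Difference 0.5 for both outcomes; SD 1.6 and r = 0.7 (HbA1c); SD 1.3 and r = 0.6 (sitting); two-sided alpha 0.025; power 80%; 125 randomised per arm less 20% attrition = 100 evaluable per arm. The analysis model is baseline-adjusted ("adjusting for baseline values, randomisation strata, and potential confounders"), so the residual SD is SD × √(1 − r²). The correlation ρ between the two test statistics is not in the document. I assume 0 to 0.5.

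**Step 1: reproduce the plan's sample size.** n per arm = 2 × (2.2414 + 0.8416)² × residual variance / 0.5², where (2.2414 + 0.8416)² = 9.505.
- HbA1c: residual variance 1.6² × 0.51 = 1.3056; n = 99.3, so 100; 100/0.8 = 125. This matches the plan.
- Sitting: residual variance 1.3² × 0.64 = 1.0816; n = 82.2, so 83; 83/0.8 gives 104.

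HbA1c sets the sample size. A change-score variance would give 147 for HbA1c, so the plan evidently used the baseline-adjusted variance.

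**Step 2: power for each outcome at 100 per arm.** Non-centrality = 0.5 / (residual SD × √(2/100)).
- HbA1c: 0.5/(1.1426 × 0.1414) = 3.094. Power is 80.3% at 0.025 and 87.2% at 0.05.
- Sitting: 0.5/(1.04 × 0.1414) = 3.400. Power is 87.7% at 0.025 and 92.5% at 0.05.

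**Step 3: Holm, with ρ = 0.** An outcome is rejected if it passes 0.025, or if it passes 0.05 and the other passes 0.025.
- HbA1c: 0.8031 + (0.8717 − 0.8031) × 0.8766 = 0.863.
- Sitting: 0.8766 + (0.9250 − 0.8766) × 0.8031 = 0.916.
- Both, fixed rule: 0.8031 × 0.8766 = 0.704.
- Both, Holm: 0.8031 × 0.9250 + 0.8717 × 0.8766 − 0.704 = 0.803.

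**Step 4: other correlations (bivariate normal).**

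| ρ | HbA1c, fixed → Holm | Sitting, fixed → Holm | Both, fixed → Holm |
|---|---|---|---|
| 0 | 80.3% → 86.3% | 87.7% → 91.6% | 70.4% → 80.3% |
| 0.3 | 80.3% → 85.9% | 87.7% → 91.0% | 72.4% → 81.3% |
| 0.5 | 80.3% → 85.7% | 87.7% → 90.5% | 74.0% → 82.2% |

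Simulation with two million draws at ρ = 0 and 0.3 agrees for the probability of both. The chance of at least one rejection is the same under either rule (97.6% at ρ = 0).

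**Step 5: familywise error for the pair (ρ = 0).**
- Both null: 1 − 0.975² = 0.049 under either rule.
- Only HbA1c null: 0.025 under the fixed rule; 0.025 + 0.025 × 0.8766 = 0.047 under Holm.
- Only sitting null: 0.025 under the fixed rule; 0.025 + 0.025 × 0.8031 = 0.045 under Holm.

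All are within 0.05.

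**The case against.** The strongest reply is that nothing here is wrong. Design and analysis use the same alpha, the rule was set in advance, the sample size follows from it, and each outcome has at least its stated 80%. That stands in full.

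A reader might infer from the 70% figure that the trial is underpowered. The documents do not support this. Nowhere does the article make success depend on both outcomes; the hypotheses concern differences in the outcomes, and an alpha split is not the design of a trial in which both must win. The case for Holm therefore rests on the gain for each outcome, about 6 points for HbA1c and 4 for sitting at ρ = 0.

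A reader might also infer that the fixed rule buys nothing in error control. It does buy something. If sitting responds and HbA1c does not, the false-positive risk on HbA1c is 0.025 under the fixed rule and about 0.047 under Holm. That scenario is plausible: the Background reports sitting reductions of 30–60 min per day in earlier trials but only modest biological effects. The 5% bound for the pair still holds.

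PAL TEA is a third primary, tested at 5% outside the pair. If only sitting is real and the other two tests are independent, the chance of a false primary claim is 1 − 0.975 × 0.95 = 7.4% now and 1 − 0.953 × 0.95 = 9.5% with Holm on the pair. So Holm does not control error across all three primaries, but the present rule does not either.

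Finally, Holm has no simple matching intervals. In the example above (HbA1c p = 0.03), a 97.5% interval would include zero although the outcome is declared significant at the second step.

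**Conclusion.** The point holds as a cheap improvement. The fixed 0.025 rule is valid, and neither the stated power nor the 125 per group is in error. With the plan's own SDs, correlations and attrition, Holm takes HbA1c power from about 80% to 86% and sitting from about 88% to between 91% and 92%. The chance of showing both rises by 8 to 10 points. Familywise error for the pair stays at or below 5%, and no participants or data are added.

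The figures rest on 100 evaluable per arm, the normal approximation, the baseline-adjusted variance that reproduces the plan's 125, and an assumed ρ of 0 to 0.5. The 5% bound for Holm does not depend on ρ.

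**What to change.** Replace the fixed threshold for the two 6-month outcomes with Holm: compare the smaller of the two p-values with 0.025; if it passes, compare the larger with 0.05; if it does not, stop. Keep the 80% as the minimum power per outcome. If the probability of showing both is reported, give it with its correlation assumption and say that it is not a success criterion.

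Report 97.5% intervals as a conservative companion, and state in advance that such an interval may include zero for an outcome declared significant at the second step. State also that the 5% for PAL TEA lies outside this rule and is unchanged by it.

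The wording is short, but the change loosens a primary threshold in a trial that has recruited since June 2019 with unblinded assessors. It therefore needs a dated, justified amendment made before any between-arm results are seen. The costs are that amendment, the greater use of the 5% when only one effect is real, and the less direct intervals.

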### Screening and consent

Screening for eligibility and gaining consent involves a multistage process. Initially, potential participants are emailed a link to a brief survey containing questions concerning eligibility. Those whose surveys indicate they may be eligible receive a follow up telephone call from research personnel to confirm. Once confirmed, participants are sent further participation information (Additional file 2), and an employer permission form via email to forward to their employer, which is completed online. This employer permission form explains the relevant study requirements and informed consent for the study and permission for installation and use of a sit-stand workstation in the workplace. Participants are requested to send a photo of their current workstation setup to assist in desk installation. If a participant is self-employed or working from home they can sign the form themselves. Thereafter, participants are asked for results of any HbA1c blood test they have had in the last 4 weeks, or are provided with a pathology request slip and asked to arrange a non-fasting blood test (glycosylated haemoglobin; HbA1c%) at their nearest Melbourne Pathology centre (at no cost to the participant). Those within the eligible HbA1c% range (6.5–10.0%) are then requested to give final informed consent (written or electronic; Additional file 2) and have their baseline visit scheduled.

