#### Cardiometabolic outcomes

A peripheral intravenous catheter is inserted near the antecubital fossa and a fasting blood sample is taken to measure glucose, serum insulin, HbA1c, high-sensitivity C-reactive protein (hs-CRP), full blood examination (FBE), cholesterol, and triglycerides. Thereafter, the participant is guided through a standard 75-g 2 h OGTT [60], with plasma glucose and serum insulin collected at half-hourly intervals. An additional volume of blood is collected for verification of results if required. Further methodological information is available in Table 4.

**Table 4 Tab4:** Brain health, cardiometabolic biomarkers and more comprehensive methodology descriptions

Cardiometabolic biomarker	Measurement methodology
Glucose	Spectrophotometric-hexokinase method using the Abbott Alinity Analyser
Insulin	Chemiluminescent Microparticle Immunoassay using the Abbott Alinity Analyser
Total cholesterol	Standard enzymatic methods using the Abbott Alinity Analyser
HDL	Accelerator Selective Detergent using the Abbott Alinity Analyser
LDL	LDL will be calculated using the Friedewald formula using the Abbott Alinity Analyser
Hs-CRP	Immunioturbidimetric method using the Abbott Alinity Analyser
HbA1c	Boranate Affinity HPLC method using the Trinity Premier Hb9210.
Full blood examination (FBE)	Beckman Coulter DXH800 instrument
TNF-α, IL-6, IL-1B, adiponectin, and leptin, BDNF,	MAGPIX multiplex microsphere-based immunoassay (Millipore, Billerica, MA)
IGF-1	Human IGF-I/IGF-1 Quantikine ELISA (R&D Systems)
Apolipoprotein E 4 (ApoE-4)	Stored in PAXgene DNA tube, PAXgene Blood DNA kits (QIAGEN) used for DNA isolation, PCR will be performed using custom design primers for the amplification of a segment of the ApoE gene and the 96-well Taqman Gene Expression qPCR Assay (Thermofisher Scientific). ApoE Sequencing (of the PCR product will occur using two single nucleotide polymorphisms (SNPs). Validation of sequencing results will be completed by targeted genotyping via differential amplification of ε2, ε3, or ε3 alleles with custom designed primer pairs.
Serum and plasma analyses	In preparation for serum analyses, samples will be collected in SST tubes and, for plasma analysis, in EDTA tubes. Both samples are rested for thirty minutes in the fridge, prior to centrifuging at 2000 RPM for 15 min at 4 degrees, with the separated plasma and serum aliquoted into 400ul and 750ul volumes and stored at −80 degrees celcius.

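### Screening HbA1c, known before randomisation, is not secured as a covariate in the HbA1c model; fixing it in would give a small efficiency gain, possibly nil

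*Protocol article*

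**What the plan says.** **Two measurements.** Under Screening and consent, a candidate supplies an HbA1c result no more than 4 weeks old or has a new test at an outside pathology centre. Entry depends on it: "Those within the eligible HbA1c% range (6.5–10.0%) are then requested to give final informed consent". Only then is the baseline visit scheduled. At that visit, under Cardiometabolic outcomes, "a fasting blood sample is taken to measure glucose, serum insulin, HbA1c". Study design and randomisation places randomisation at the end of the baseline assessment. Both results therefore precede allocation.

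**The model.** Statistical analyses specifies mixed models "accounting for repeated measures, adjusting for baseline values, randomisation strata", and also potential confounders. These are drawn from the literature and reduced by backward elimination, which always keeps age and sex and otherwise keeps variables associated with the outcome at p < 0.2. Screening HbA1c is neither named nor excluded.

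**The COVID pathway.** When restrictions applied, the clinic blood draw was replaced by an off-site pathology HbA1c test (Clinical assessment; Table 2, footnote a). The article does not say whether this is a different test from the screening one.

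**The concern.** A single HbA1c reading carries assay error and short-term variation. A second pre-randomisation reading can remove part of that noise from the treatment comparison. It cannot be affected by allocation, and selecting participants on it does not make it invalid as a covariate.

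The rule as written does not reliably bring it in. A repeat reading of the outcome is not a confounder in the usual sense, so a literature search may not list it. If it were listed, it could still be eliminated, because only age and sex are protected.

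HbA1c is where extra precision would be most useful. It sets the sample size, it has almost no slack above 80% power, and the Sample size section allows recruitment to end below target.

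**Working it through.** **Inputs from the Sample size section**
- Significance level: "2-tailed significance of 2.5% (correcting for two primary outcomes for the original OPTIMISE protocol"), so z = 2.2414; for 80% power, z = 0.8416.
- Differences: "minimum differences of interest in HbA1c and sitting of 0.5% and 0.5 h/16 h-day".
- Spread: "assuming standard deviations (SD) of 1.6 and 1.3 and a pre-post correlation (r) of 0.7 and 0.6 respectively".
- Attrition: "With an estimated 20% attrition based on our previous intervention trials".
- Target: "125 participants per group (250 total) are required for 80% power".

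**Step 1: reproduce the plan's figure.** With adjustment for one baseline value,

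n = 2 × (2.2414 + 0.8416)² × SD² × (1 − r²) / δ², then divide by 0.80 for attrition.

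- HbA1c: 2 × 9.505 × 2.56 × 0.51 / 0.25 = 99.3, so 100 evaluable and 125 randomised per arm. This matches exactly.
- Sitting: 2 × 9.505 × 1.69 × 0.64 / 0.25 = 82.2, so 83 evaluable and 104 randomised per arm.

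HbA1c therefore sets the sample size. Its power at 100 evaluable per arm is Φ(0.5 / √(2 × 2.56 × 0.51 / 100) − 2.2414) = 80.3%.

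**Step 2: add the screening value.** Let r = 0.7 be the baseline to month-6 correlation (from the plan), ρ the screening-baseline correlation and s the screening to month-6 correlation. The article gives neither ρ nor s, so both are assumptions here.

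R² = (r² + s² − 2·r·s·ρ) / (1 − ρ²), and the residual variance fraction is 1 − R², against 0.51 with baseline alone.

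*Favourable case: screening predicts month 6 as well as baseline does (s = 0.7).* The formula reduces to R² = 2 × 0.49 / (1 + ρ).

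| ρ | Residual fraction | Fall in residual variance | Evaluable per arm | Randomised per arm | Power at 100 evaluable per arm |
|---|---|---|---|---|---|
| 0.80 | 0.456 | 10.7% | 89 | 112 | 84.9% |
| 0.85 | 0.470 | 7.8% | 92 | 115 | 83.7% |
| 0.90 | 0.484 | 5.1% | 95 | 119 | 82.5% |
| 0.95 | 0.497 | 2.5% | 97 | 122 | 81.4% |

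*Intermediate case: s halfway between ρ × r and r.* For ρ from 0.95 to 0.80, the fall is 0.6% to 2.7%, the requirement is 124 to 122 per arm, and power is 80.6% to 81.5%.

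*Slightly weaker screening value: s = 0.65 with ρ = 0.90.* R² = (0.49 + 0.4225 − 0.819) / 0.19 = 0.492. The residual fraction is 0.508, a fall of 0.4%, and power is about 80.5%.

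*No gain: s = ρ × r.* The residual fraction stays at 0.51, the requirement at 125 per arm and power at 80.3%.

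Values of ρ below 0.80 are not carried forward. At ρ = 0.70 two readings taken shortly apart would agree no better than the plan assumes for readings before and after the intervention.

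These figures use the plan's single-time-point formula and not the full repeated-measures model.

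**The case against.** The strongest objection is that nothing here is wrong. Baseline adjustment is standard and unbiased, and the sample size was built on exactly that model. A condensed article may also leave the full covariate list to an analysis plan that is not shown. All of that stands, and it limits this point to an optional improvement.

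The second objection is that screening may be the weaker predictor. It is the earlier reading, it may come from another laboratory or assay, and entry truncates it to 6.5–10.0%, which can lower its correlation with later values. This also stands, and it is why zero has to be the lower end of the range. It does not make the covariate invalid.

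Two stronger readings are tempting, and the article supports neither:
- A reader might infer that every participant has two separate values. The COVID pathway leaves open that one pathology test served as both screening and baseline, and for those participants there is nothing to gain.
- A reader might infer that the model adjusts for baseline HbA1c only. Strata and confounders also enter, and the screening value is not excluded. What the text supports is that it is not named and not protected from elimination.

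**Conclusion.** The point holds as a low-priority efficiency gain. Under the standard pathway a second valid pre-randomisation HbA1c is available, and the stated covariate rule does not secure its use. The baseline-only analysis remains valid, and the trial has its planned power under the plan's own assumptions.

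The benefit rests wholly on ρ and s. Across the cases considered it runs from nothing to about 11% of residual variance. For two tests taken close together, ρ of 0.85 or more is the more plausible region, so the realistic expectation is 0 to 3.5 power points. The average over the trial would be lower still if many participants had one test serving as both.

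**What to change.** In the HbA1c model, pre-specify screening HbA1c as a fixed covariate, exempt from the p < 0.2 elimination. It sits alongside baseline HbA1c, the medication stratum, age, sex and whatever other confounders the plan's rule retains. Possible wording: *The HbA1c model will include baseline HbA1c and screening HbA1c, both measured before randomisation, as fixed covariates together with stratum, age and sex; other confounders are selected as described.*

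Add a sentence on participants whose remote baseline test is the screening test. One workable option is to enter the same value for both and include an indicator for a single test. Settle this before outcome data are analysed, so that the choice cannot look data-driven.

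The cost is one or two model terms and some data work. The numeric screening values have to be taken from the eligibility records (Table 2 does not list them as a collected research variable), duplicate tests identified, and the laboratory of origin noted where known. Recruitment, visits and the stated sample size do not change.

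### Covariates for the main randomised comparison are chosen by backward elimination on the trial's own outcomes, so the primary model is not fixed in advance

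*Protocol article*

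**What the plan says.** In the protocol article, Statistical analyses, the between-arm comparisons of primary and secondary outcomes use mixed models, "accounting for repeated measures, adjusting for baseline values, randomisation strata, and potential confounders". The last of these terms is defined in two stages. First, candidates are taken from the literature beforehand. Second, they are "narrowed down to a number that can be modelled without overfitting, based on an objective criterion not open to manipulation", and the criterion is given in brackets: "backwards elimination: retaining age, sex, and *p* < 0.2 association with the outcome".

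The same section sets two-sided significance at 0.05, "except for *p* < 0.025 when testing co-primary outcomes based on α = 0.025". This matches the Sample size section, which uses "2-tailed significance of 2.5% (correcting for two primary outcomes for the original OPTIMISE protocol").

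The article does not say whether arm is in the model while covariates are being eliminated, or whether one covariate set is shared across outcomes.

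**The concern.** The elimination step looks at the association between each candidate and the outcome in the data being analysed. The covariate set of the primary model is thus a result of the trial and not part of its design. The article presents the rule as protection against overfitting and manipulation, but a p < 0.2 filter lets in variables that fit by chance, and the fitted model is then reported as if it had been chosen beforehand.

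Two things are at stake. The first is that the primary analysis cannot be written down before outcome data exist, and HbA1c, sitting and PAL TEA are likely to be adjusted for different variables. The second is that, in one version of the procedure, the test of arm rejects too often. In a randomised comparison there is little to set against this: randomisation deals with confounding in expectation, and the gain from adjustment comes from baseline prognostic variables, which can be named in advance.

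**Working it through.** **1. The plan's own sample size (Sample size section).** Inputs: two-sided α 0.025, power 80%, HbA1c difference 0.5 with SD 1.6 and r 0.7, sitting difference 0.5 with SD 1.3 and r 0.6, attrition 20%. With adjustment for baseline only, n per arm = 2(z₀.₉₈₇₅ + z₀.₈)² · SD²(1 − r²)/d².

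- HbA1c: 2 × (2.241 + 0.842)² × (2.56 × 0.51)/0.25 = 19.01 × 5.222 = 99.3, so 100; 100/0.8 = 125. This matches the stated 125 per group.
- Sitting: 19.01 × (1.69 × 0.64)/0.25 = 82.2, so 83; 83/0.8 = 104. HbA1c drives the size.
- PAL TEA (80 per arm, α 0.05, d = 0.33, r = 0.7): SE = √0.51 × √(2/80) = 0.113; 0.33/0.113 − 1.96 = 0.96, which gives 83% power. This agrees with the stated figure of more than 80%.

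No covariate beyond the baseline value is needed for the stated power.

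**2. How much noise the rule keeps.** A candidate unrelated to the outcome passes p < 0.2 about 20% of the time, so about 0.2k of k noise candidates stay: 2 of 10, 4 of 20. The simulated averages were 2.1 and 4.3–4.4.

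**3. Type I error.** Simulation under no treatment effect: one follow-up time; linear model with arm, baseline (r = 0.7), two forced covariates standing for age and sex, and a binary stratum; independent candidates eliminated backward at p ≥ 0.2. The number of candidates is an assumption. Each cell shows rejection (%) at nominal 2.5% / 5%.

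| Evaluable per arm | Candidates | Arm in elimination | Arm left out | All candidates kept | Forced terms only |
|---|---|---|---|---|---|
| 100 | 5 noise | 2.7 / 5.2 | 2.5 / 5.0 | 2.5 / 5.0 | 2.4 / 5.1 |
| 100 | 10 noise | 3.1 / 5.8 | 2.7 / 5.2 | 2.7 / 5.2 | 2.7 / 5.2 |
| 100 | 10, of which 5 prognostic | 2.9 / 5.7 | 2.6 / 5.1 | 2.5 / 5.2 | 2.6 / 5.0 |
| 100 | 20 noise | 3.1 / 6.4 | 2.4 / 4.9 | 2.6 / 5.2 | 2.6 / 5.2 |
| 80 | 10 noise | 2.8 / 5.5 | 2.4 / 4.9 | 2.5 / 4.9 | 2.4 / 4.8 |
| 80 | 20 noise | 3.6 / 6.5 | 2.5 / 5.1 | 2.7 / 5.0 | 2.4 / 5.1 |
| 80 | 30 noise | 4.5 / 8.4 | 2.8 / 5.6 | 2.7 / 5.4 | 2.6 / 5.2 |

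Runs per row: 5,000 (last row) to 20,000. The Monte Carlo SE at 2.5% is √(0.025 × 0.975/20,000) = 0.11 points with 20,000 runs and 0.22 points with 5,000.

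Further simulations of the same kind (4,000–6,000 trials per cell), with arm in the elimination model, gave:

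- 200 evaluable, nominal 2.5%: 2.7–2.9% with 10 candidates, 3.3–3.5% with 20.
- 160 evaluable, nominal 5%: 6.0–6.2% with 15 candidates, 6.6–7.3% with 25.

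With arm left out they gave 2.2–2.7% and 4.6–5.8%. In the cell with 5.8%, the forced-terms model gave 5.7% in the same runs, so that value is simulation chance.

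**4. Standard errors, arm in elimination.** Mean reported SE over true SD of the estimate was 0.1013/0.1032 and 0.1005/0.1074 (200 evaluable, 10 and 20 candidates), and 0.1128/0.1193 and 0.1117/0.1216 (160 evaluable, 15 and 25). The reported SE is thus about 2%, 6%, 5% and 8% too small. With arm left out it matched the fixed model.

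**5. Why arm matters.** Under no effect, outcome and candidates are independent of the randomised arm. A set chosen from outcome and candidates alone is also independent of arm, so the later test keeps its level. Once arm is in the elimination model, the chosen set depends on the allocation and that argument fails.

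**6. Agreement between outcomes.** For two outcomes selecting independently, a noise candidate is treated alike with probability 0.2² + 0.8² = 0.68, so ten are treated alike with probability 0.68¹⁰ = 0.021. Simulation with an assumed error correlation of 0.3 also gave about 2%.

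**The case against.** The strongest reply is that the rule already limits discretion. Candidates are set beforehand, age and sex are forced in, baseline and strata are always adjusted for, and the threshold is fixed. That is a fair reading of the claim that the rule cannot be manipulated, and it stands as far as it goes. It does not answer the point that the final set is driven by outcome data.

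A reader might infer more than the article supports:

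- **That the plan inflates type I error and gives intervals that are too narrow.** This holds only if arm is in the elimination model, and the article is silent on that. With arm left out, rejection was nominal within simulation error. Even with arm in, the excess is small for a short list and partly within simulation noise: near 2.8%, 6,000 runs have an SE of about 0.2 points.
- **That the model depends on unblinded data.** Elimination without arm needs no allocation codes. The Study design and randomisation section says participants and assessors cannot be blinded; it says nothing about the analyst.
- **That different covariates per outcome are an error.** The article does not say whether a set is shared, so the difference is inferred from the wording about association with the outcome. Different sets named in advance would be acceptable.
- **That the candidate list is missing.** It may sit in an analysis plan that is not shown. A list would not cure the point, because the selection step would remain.

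Large noise pools may also look unfair, since candidates drawn from the literature should include prognostic variables. With 5 of 10 prognostic, the unfavourable version still gave 2.9% and 5.7%. Pools of 10–25 are plausible: the Dietary intake section treats a multi-component diet report as confounding variables, and the Medication and allied health appointments section adds more.

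**Conclusion.** The point holds in a limited form. The main randomised comparison uses covariates selected on the trial's own outcomes, so the primary model is not fixed until outcome data are seen and will normally differ between the three primary outcomes. The stated rationale is mistaken: the rule keeps about a fifth of noise candidates, while keeping every candidate held the nominal level in the same simulations.

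The effect on error rates is conditional and modest. With arm in the elimination model, type I error is about 2.7–3.5% at nominal 2.5% (200 evaluable, 10–20 noise candidates) and 6–7% at nominal 5% (160 evaluable, 15–25 noise candidates). With arm left out there is no detectable inflation. These figures rest on assumed pool sizes, independent candidates and one follow-up time in place of the full repeated-measures model. This is something the sponsor should correct; it does not invalidate the design.

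**What to change.** Remove the elimination step from the main analysis. Adjust every between-arm comparison for the baseline value of the outcome, medication stratum, age, sex and any further prognostic covariates named before outcome data are examined. Restrict these to baseline values, since Table 2 shows that diet and medication are also recorded at follow-up. How many covariates to name is the sponsor's choice. Any selected-covariate model becomes a sensitivity analysis, with a statement of whether arm is in the model during selection.

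The cost is about one sentence of analysis text and less analysis work. The downside is a possible small loss of precision if a useful prognostic variable is left off the list. The target of 125 per arm needs no change, because it follows from baseline adjustment alone.
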